### Control group program

Control subjects will receive the standard of care according to the SRS criteria: observation for patients with curves between 10 degrees and 25 degrees [9] and attendance at the study assessments. The control group will only attend study assessments and not the therapy sessions.

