### Compliance supervision

Compliance will be monitored using a home training diary to record the time and frequency of every-day home training, verified daily by a parent and weekly by a therapist. Meanwhile, all the patients will be added to Micro Message Platform app created by the research assistant. The assistant will divide the patients into two groups following their allocation and check the daily training at irregular intervals, answer patients’ questions online, share health knowledge with the patients, or remind the patients to attend clinic visits after the 6-month intervention. To maximize compliance, the physical therapist will provide home equipment, provide the patients with access to facilities, change the exercises to improve compliance with exercises to avoid patients’ getting bored with always performing the same exercises, and encourage parents to be fully engaged to ensure the exercises are regularly performed at home. Attendance will be calculated as a percentage of the prescribed visits attended, and compliance will be calculated as a percentage of the prescribed home exercise dose completed over the course of the 6 months of treatment. When compliance drops below 70%, the physical therapist will try to resolve the issues cooperatively with patients and parents [29, 30].

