### Assessment

The following demographic data and patient characteristics of the experimental group will be collected: age, gender, height, weight, body mass index, Risser sign, time since menarche for female patients, curve pattern, apex levels, and exercise compliance. Skeletal immaturity based on the Risser stages will be recorded for each patient at the first assessment. Curvatures will be classified according to the Ponseti classification system, which distinguishes four major types of scoliosis: thoracic, lumbar, thoracolumbar, and S-shaped [8, 33]. Development of the ossification of the iliac crest is used to assess the remaining spinal growth, and the stage of ossification of the iliac apophysis can be seen on a radiograph. The Risser sign is an assessment of skeletal maturity and spinal growth. It is based on the ossification of the iliac apophysis, which is evaluated with a four-grade scale from 0 (no ossification) to 5 (fused ossified apophysis) [34]. The outcome measures described in the subsections that follow will be performed before and after 6 months of intervention in both groups.

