### Data collection, data management, and statistical analysis plan

The primary outcome is the change of Cobb angle, and the secondary outcome measures will include the ATR, sagittal index, and quality of life. Descriptive statistics will be calculated for baseline demographics, physical examination, radiographs, and questionnaire data, and results will be presented as the mean ± SD, whereas categorical variables will be expressed as percentages. The chi-squared test will be used to compare the categorical/dichotomous variables. Separate analyses will be conducted for each outcome.

Data will be entered using EpiData software designed for this study. All data will be collected, typed, and analyzed by a masked statistician who will not have access to study assignment. The main investigators will check the data every 2 weeks to ensure the quality.

The primary endpoint is the pre- and posttreatment difference in the Cobb angle. We have calculated that a sample size of 21 patients per group would be capable of detecting a between-group difference of 5 degrees in the primary endpoint with a type I error of 5% and a power of 95% [20]. Because the interval of Cobb angles at entry is 10–20 degrees, and assuming a uniform distribution of Cobb angles in this range (the most unfavorable scenario), an SD of 5 degrees is estimated [8].

Baseline comparability will be assessed using Student’s *t* test for independent samples. To screen for variables associated with each of the outcome variables, univariate linear mixed models for each relevant covariable (age, gender, body mass index, Risser sign, time since menarche, apex levels, curve pattern, and compliance may have associations with risk of progression) will be conducted.

Multiple linear mixed models for each time point will be tested, including covariables found significant at *p* ≤ 0.20 in the univariate analysis, and after screening for multicollinearity [42].

For the ordinal outcome (SRS-22, which is based on only one item with five levels), generalized linear mixed effects model analysis will be used.

Furthermore, because subjects with younger than 13 years of age are characterized by a higher risk of progression [43], the patients will be divided into two subgroups (age < 13 years and age ≥ 13 years), and a linear mixed model analysis for the primary outcome will be performed on each subgroup.

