To assess differences in group changes from baseline to 6 months while adjusting for covariables, weighted estimating equations and a sensitivity analysis will be conducted as the primary approach to deal with the missing data, especially for the primary outcome of Cobb angle [44]. All the analysis will be carried out using IBM SPSS Statistics for version 20.0 software (IBM, Armonk, NY, USA).

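### Exercise compliance, measured after randomisation and defined only in the exercise arm, should not be a candidate covariable in the between-group models

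*Protocol article*

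**What the plan says.** All references are to the protocol article.

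- **Data collection, data management, and statistical analysis plan.** Eight covariables are screened one at a time against each outcome: age, gender, body mass index, Risser sign, time since menarche, and then "apex levels, curve pattern, and compliance may have associations with risk of progression". Those that reach the threshold of p ≤ "0.20 in the univariate analysis, and after screening for multicollinearity" enter the multiple linear mixed models. The section closes with the purpose of adjustment: "To assess differences in group changes from baseline to 6 months while adjusting for covariables".
- **Compliance supervision.** The definition is: "compliance will be calculated as a percentage of the prescribed home exercise dose completed over the course of the 6 months of treatment". It is also acted on during treatment: "When compliance drops below 70%, the physical therapist will try to resolve the issues".
- **Control group program.** Controls are observed: "The control group will only attend study assessments and not the therapy sessions". The daily home session is described under the experimental programme only.
- **Assessment.** Exercise compliance ends a list introduced by the words "demographic data and patient characteristics of the experimental group will be collected".

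Nothing in the article confines compliance to an analysis within the exercise arm or exempts it from the between-group models.

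**The concern.** Adjustment in a randomised trial is safe for variables fixed before allocation. Compliance is generated by the treatment period, and it has a denominator only where exercise was prescribed. Two codings are open for controls, and neither works in a model that compares the arms.

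- **Missing.** Every control is an incomplete case, so the group term has nothing to be compared with.
- **Zero.** The variable separates the arms almost perfectly. It also measures the exercise through which the treatment is meant to work. The group coefficient then describes what is left of assignment once the exercise done is held fixed, which is not the question the trial was randomised to answer.

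The selection rule makes matters worse. Coded as zero, compliance carries the group difference in the univariate screen, so the better the treatment works, the more surely it is selected. At stake is the covariable-adjusted estimate of the group difference in Cobb angle change.

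**Working it through.** **The plan's own figure.** Inputs from the section headed Sample measurement: change of −1.55 (SD 4.39) with exercise and 2.90 (SD 2.60) in controls, α = 0.05, β = 0.05.

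- Difference: 2.90 + 1.55 = 4.45 degrees.
- Pooled SD: √((4.39² + 2.60²)/2) = √13.016 = 3.608, so d = 4.45/3.608 = 1.233.
- A two-sided two-sample t test with 19 per group has 95.9% power. The stated 19 is reproduced.
- With 21 per arm, the unadjusted standard error is 3.608 × √(2/21) = 1.11 degrees, and simulated power is about 97%.

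**Compliance missing in controls.** Complete cases are at most 21 exercise patients and 0 controls. Group is then constant and its effect cannot be estimated. The planned weighting for missing data cannot repair this, because no control has an observed value to weight up.

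**Compliance coded 0 in controls.** The documents give no distribution, so these are assumptions: exercise-arm mean m of 60–80% and SD s of 10–25 points before truncation to 0–100. The protocol's 70% action level makes this range plausible but does not fix it.

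Because compliance varies only within the exercise arm, the variance inflation factor (VIF) for group is approximately

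VIF = 1 + n·m² / (2(n − 1)·s²), with n = 21.

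- m = 80, s = 10: 1 + 21 × 6400/(40 × 100) = 34.6; SE ≈ 1.11 × √34.6 ≈ 6.5 degrees.
- m = 60, s = 25: 1 + 21 × 3600/(40 × 625) = 4.0; SE ≈ 1.11 × √4.0 ≈ 2.2 degrees.

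Truncation narrows the spread, so simulated values are somewhat higher. The simulation used 3,000 trials per setting, 21 per arm, and least squares of change on group and compliance. The share of the 4.45-degree benefit that acts through the exercise done was set at 0, 50 or 100%. The last three columns give the adjusted group effect in degrees and, in brackets, the proportion of trials with p < 0.05.

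| Mean, SD (%) | Mean VIF | Passes p ≤ 0.20 | SE | 0% share | 50% share | 100% share |
|---|---|---|---|---|---|---|
| 80, 10 | 40 | 99.4–99.7% | 6.8 | −4.71 (16.7%) | −2.23 (12.2%) | −0.09 (9.7%) |
| 80, 15 | 20 | 99.2–99.7% | 4.9 | −4.49 (19.9%) | −2.26 (12.8%) | 0.01 (10.5%) |
| 70, 20 | 9 | 99.0–99.6% | 3.2 | −4.32 (29.9%) | −2.31 (15.8%) | 0.01 (9.8%) |
| 60, 25 | 5 | 97.3–99.7% | 2.4 | −4.45 (47.5%) | −2.21 (19.1%) | 0.00 (9.5%) |

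A repeat of the exercise gave an SE of up to 7.1 degrees and a highest power of 46%, so the ranges are best read as about 2.4–7 degrees and about 10% to just under 50%.

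The last column is not power. The coefficient there is zero, yet the test rejects in about 10% of trials. The compliance slope is estimated from the exercise arm alone, whose variance is 4.39² = 19.27, while the model uses the pooled 13.02. The true SE is therefore about √(19.27/13.02) = 1.22 times the reported one. The critical value of 2.02 acts like 2.02/1.22 = 1.66, which on 39 degrees of freedom corresponds to about 10%.

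**Would the multicollinearity screen catch it?** With a cut-off of VIF > 10 and mean 80%, compliance would be flagged in nearly all trials at SD 10 or 15, roughly three quarters at SD 20 and roughly a third at SD 25. At mean 60% and SD 25 it would be flagged in about 1%.

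**The case against.** The best defence is the plan's own safeguard. Covariables enter only after a multicollinearity check, and the settings with the largest loss of power are those that a conventional cut-off would most reliably catch. This stands in part: the power figures hold only if compliance is retained. But no threshold is given, and at the low end of the range a cut-off of 10 would almost never act.

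Second, the multivariable model is not named as the primary test. The sample size rests on two group means, and the Interim analysis section defines the effect size from the difference in mean change, with no covariables. This stands. A reader might infer that the trial's primary comparison is lost; the documents do not support that, because the unadjusted difference is unaffected.

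Third, a loss of precision is not a bias. This also stands: if none of the benefit acts through the exercise done, the adjusted effect stays near −4.4 degrees. Attenuation needs an assumed mediated share, which no document supplies.

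Three further readings are tempting and do not hold.

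- **No covariates exist for controls.** Read literally, the Assessment section collects characteristics in the experimental group only. But Randomization and masking places baseline data collection before allocation, the Assessment section itself records Risser stage for every patient, and baseline comparability is to be tested between groups. For the baseline variables the phrase is a drafting slip.
- **The screen might drop the group variable.** Group is not on the covariable list, and dropping it would defeat the stated purpose of the model.
- **Time since menarche has the same fault.** It is a baseline variable. How to code it for patients without a value is a detail commonly left to the analysis plan, which is not shown.

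Leaving compliance itself to that analysis plan is no answer. The protocol already names it as a covariable, so an analysis plan could correct this only by departing from the protocol.

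**Conclusion.** The covariable list is wrong as written. Compliance arises after randomisation, has no meaning for controls, and is offered to models whose purpose is to compare the arms. Under missing coding the adjusted group effect cannot be estimated; this needs no assumption beyond complete-case fitting. Under zero coding the coefficient is no longer the effect of assignment. Its precision loss depends on the assumed compliance distribution and on compliance surviving an unspecified screen. Its attenuation, to about −2.2 degrees if half the benefit acts through the exercise done and to about 0 if all of it does, depends on an assumed mediated share.

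Severity: should be fixed. The damage is confined to the covariable-adjusted models, and a conventional collinearity check might remove compliance, but the plan should not depend on that.

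**What to change.** - Delete compliance from the covariables of all between-group models, and state that adjustment uses baseline variables only.
- Report compliance descriptively within the exercise arm. If a relation with outcome is wanted, examine it there in a dose-response analysis labelled exploratory.
- As a wording correction only, change the Assessment section so that the baseline characteristics are collected in both groups, and keep exercise compliance as an item of the exercise arm.

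The cost is a protocol and analysis plan wording change. No data, visits or patients are added or lost, and the sample size is unaffected. Recruitment has begun, so the change should be dated and made before any comparison by arm, including the interim analysis.

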### Sample measurement

G*Power 3.1.9.2 was used to perform the power calculations. The change of Cobb angle was the primary outcome measurement. The results of our previous study showed that the change of Cobb angle in the experimental group was − 1.55 ± 4.39 degrees, whereas in the control group, it was 2.90 ± 2.60 degrees [25]. The α will be 0.05, and the β will be 0.05. Therefore, we should recruit 19 patients to each group. Considering 10% potential attrition, 21 patients per group will be recruited.

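### The primary endpoint is change in Cobb angle, but the adjusted models are specified per time point and the change is given to another method; no deciding test is named, and a literal 6-month comparison may lack the planned 95% power

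*Protocol article*

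**What the plan says.** In the protocol article, the section *Data collection, data management, and statistical analysis plan* defines the endpoint: "The primary endpoint is the pre- and posttreatment difference in the Cobb angle". *Interim analysis* repeats that the change is the sole primary outcome. *Sample measurement* sizes the trial on change scores from the group's previous study: "the change of Cobb angle in the experimental group was − 1.55 ± 4.39 degrees", "whereas in the control group, it was 2.90 ± 2.60 degrees". The error rates are given as "The α will be 0.05, and the β will be 0.05", and the result follows: "Therefore, we should recruit 19 patients to each group". *Randomization and masking* and *Assessment* provide two measurement occasions only, baseline and 6 months.

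Two adjusted analyses are then described.

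- After a univariate screen: "Multiple linear mixed models for each time point will be tested, including covariables found significant at" p ≤ 0.20. The candidates are age, gender, body mass index, Risser sign, time since menarche, apex levels, curve pattern and compliance. Baseline Cobb angle is not among them.
- In the last paragraph of the section, between-group differences in the change from baseline to 6 months, adjusted for covariates, are assigned to a different method: "weighted estimating equations and a sensitivity analysis will be conducted as the primary approach to deal with the missing data".

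**The concern.** An endpoint defined as a change calls for an analysis of the change, or an analysis of the 6-month value adjusted for baseline. Separate models at each of two visits, without baseline Cobb angle, are neither. Each would hold one Cobb value per patient, which leaves no repeated measure for a patient-level random effect. The baseline model would compare the arms before treatment and so cannot show a treatment effect. The 6-month model would carry the spread of entry angles that a change score removes.

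The change does have a method, in a separate paragraph, but the article does not rank the two analyses. Two things are at stake. The analysis that is reported as primary may have less power than the sample size was built to give. And if the choice is left until results are known, two correlated tests at 5% are available for one primary claim.

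**Working it through.** **Inputs from the protocol article.** Mean change −1.55 (SD 4.39) in the experimental arm and +2.90 (SD 2.60) in the control arm; α = 0.05, power 0.95; 19 evaluable per arm (*Sample measurement*). Entry Cobb angle 10–20 degrees, taken as uniform, with a stated SD of 5 (*Data collection, data management, and statistical analysis plan*).

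**Inputs not in the article (assumed).** The correlation r between baseline Cobb angle and change, shown over a range. For the baseline SD two values are used: 10/√12 = 2.89, the SD of a uniform 10–20 distribution, and the article's 5. A distribution confined to 10–20 degrees cannot have an SD above half its range, which is 5, so the second value is an extreme.

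**Step 1: reproduce the plan's figure.**
- Difference = 2.90 − (−1.55) = 4.45.
- Pooled SD of change = √((4.39² + 2.60²)/2) = √13.02 = 3.61.
- d = 4.45/3.61 = 1.233.
- A two-sided t test (noncentral t, df = 36, noncentrality d·√(19/2) = 3.80) has power 0.959 at 19 per arm and 0.949 at 18. The stated 19 is reproduced as a two-sided test on the change.

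**Step 2: the 6-month level, not adjusted for baseline Cobb angle.** In each arm the variance is SD_base² + SD_change² + 2·r·SD_base·SD_change. Averaged over the arms this is SD_base² + 13.02 + r·SD_base·(4.39 + 2.60). The effect is the same 4.45 degrees.

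| Baseline SD | r | SD at 6 months | d | Power, 19 per arm |
|---|---|---|---|---|
| 2.89 | +0.3 | 5.23 | 0.85 | 0.722 |
| 2.89 | 0 | 4.62 | 0.96 | 0.823 |
| 2.89 | −0.3 | 3.91 | 1.14 | 0.927 |
| 2.89 | −0.4 | 3.64 | 1.22 | 0.956 |
| 5 | 0 | 6.17 | 0.72 | 0.581 |
| 5 | −0.3 | 5.25 | 0.85 | 0.720 |
| 5 | −0.6 | 4.13 | 1.08 | 0.898 |

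At r = 0, 95% power would need 30 per arm (SD 2.89) or 51 per arm (SD 5).

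**Step 3: where the two contrasts have equal power.** Set SD_base² + r·SD_base·6.99 = 0, so r = −SD_base/6.99. This gives −0.41 for SD 2.89 and −0.72 for SD 5. At a less negative correlation, the level contrast is the weaker one.

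**Step 4: adjusting for baseline Cobb angle.** The residual SD becomes 3.61·√(1 − r²), never larger than the SD of change. Power at 19 per arm is then about 0.96 or more for every r examined (−0.6 to +0.5), apart from the loss of one degree of freedom.

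**Step 5: false-positive rate if either test could count.** With no effect, the two test statistics have correlation ρ = (SD_change² + r·SD_base·SD_change)/(SD_6m·SD_change). For SD 2.89 and r = 0, ρ = 3.61/4.62 = 0.78, and the chance that at least one is significant at two-sided 5% is 0.079 (bivariate normal). For r from −0.3 to +0.3 the range is 0.075–0.083 with SD 2.89 and 0.082–0.093 with SD 5.

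**The case against.** The strongest reply is that this is loose wording. Authors who write of linear mixed models may mean time-specific contrasts within one repeated-measures model, and the group-by-time term of such a model is the change. The change is named consistently as the primary outcome, and nothing states that 6-month levels will be tested as the primary endpoint. An article also commonly leaves model form and the ranking of analyses to a fuller document. This stands in part: the wording does not settle which models are meant, and under the repeated-measures reading the power loss disappears. Even so, the article itself states two adjusted analyses that can bear on the primary endpoint, and one of them, as worded, does not match it.

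Four stronger readings are tempting and should be resisted.

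- *The estimating equations are named the primary analysis of change.* The sentence opens with assessing change, but the word primary attaches to handling missing data. Nor does the article call the per-time-point models its main analysis.
- *Only the change contrast has the planned power.* This depends on a correlation that the article does not report. At r = −0.4 with baseline SD 2.89, both contrasts reach about 96%. Moreover, the article's second power statement (5 degrees, SD 5, 21 per arm) gives about 89% two-sided for the change itself.
- *The two analyses estimate different effects.* Under randomisation both target the same expected treatment effect. They differ in precision and in exposure to chance baseline imbalance, so one may be significant and the other not.
- *The plan allows success on either test.* It does not say so. The 7.5–9% applies only if the choice were left open in practice.

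**Conclusion.** The point holds as a mismatch that should be corrected before unblinding. The endpoint and sample size rest on the change, the adjusted models as literally worded address visit-specific levels without baseline Cobb angle, the change is given to another method, and the deciding result is not identified.

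On the literal reading, and with the effect and change SDs of *Sample measurement*, power at 19 per arm falls from about 96% to about 82% when baseline (SD 2.89) and change are uncorrelated. The range is 72% to 96% for r from +0.3 to −0.4, and about 58% at r = 0 with the extreme baseline SD of 5. The loss is therefore possible, and under zero or positive correlation substantial, but it is not established by the article. The data to be collected are unaffected.

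**What to change.** Replace the per-time-point models for Cobb angle with one prespecified primary model of the difference in 6-month change. Either of two forms would do:

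- a linear mixed model containing both visits, with arm, time and arm-by-time, in which the arm-by-time term is the test (with complete data, this is the contrast that the sample size was built on); or
- 6-month Cobb angle, or its change, by arm with baseline Cobb angle as a covariate, in which the arm term is the test.

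State that this contrast, at two-sided 5%, is the only test that decides the trial, and label the weighted estimating equations a sensitivity analysis for missing data.

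The cost is two or three sentences. No further data or patients are needed, and mixed models are already planned. The small downside is that the estimating-equation result no longer offers a second route to a positive primary claim.

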#### SRS-22 dimension scores

The 22-item Scoliosis Research Society Outcomes Questionnaire (SRS-22) is especially designed for patients with idiopathic scoliosis [24]. The questionnaire consists of 22 items with 5 dimensions: function/activity, pain, self-image, mental health, and satisfaction with treatment. Each domain has five items each, except the satisfaction with treatment domain, which has only two items. The two satisfaction items are not included in the final analysis. Each item is scored from 1 (worst) to 5 (best). Results are presented as the mean of each scale (sum of 5 questions/5) and the mean subtotal score (sum of 20 questions/20) [39, 40]. In this study, we will use the validated Chinese version of SRS-22 [41].

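### The SRS-22 is assigned an ordinal analysis because it is described as a single five-level item, but the protocol's own scoring makes it a set of 5-item and 20-item means

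*Protocol article*

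**What the plan says.** Two sections of the protocol article describe the SRS-22.

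- **SRS-22 dimension scores** defines the outcome. "The questionnaire consists of 22 items with 5 dimensions: function/activity, pain, self-image, mental health, and satisfaction with treatment". On the item count: "Each domain has five items each, except the satisfaction with treatment domain, which has only two items". On what is analysed: "The two satisfaction items are not included in the final analysis". Items are scored 1 to 5. On the reported scores: "Results are presented as the mean of each scale (sum of 5 questions/5) and the mean subtotal score (sum of 20 questions/20").
- **Data collection, data management, and statistical analysis plan** plans univariate and then multiple linear mixed models for the outcomes in general, and then makes an exception: "For the ordinal outcome (SRS-22, which is based on only one item with five levels), generalized linear mixed effects model analysis will be used".

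The same statistical section also covers how questionnaire responses are summarised: "questionnaire data, and results will be presented as the mean ± SD, whereas categorical variables will be expressed as percentages". Quality of life is listed there as a secondary outcome, and it is one of the four effects named in the aims.

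**The concern.** The exception for the SRS-22 rests on a statement about the structure of the scale, and the outcome definition contradicts that statement. An analyst following the statistical section would look for one item with five ordered categories. An analyst following the outcome definition would have five mean scores per patient and visit. The two instructions cannot both be followed.

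The analysis of a stated objective is at stake. Depending on which section is followed, the result could be a difference in SRS-22 points or an effect on an ordinal scale. Leaving this unsettled lets the model be chosen after the data are seen, for a patient-reported outcome in patients who know their allocation. The problem is not missing detail that an analysis plan would normally supply: the protocol states the structure of the outcome wrongly and chooses a model on that basis.

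**Working it through.** **Inputs, all from the section on SRS-22 dimension scores unless noted**

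- Four domains of 5 items and one domain (satisfaction) of 2 items.
- The 2 satisfaction items are left out of the analysis.
- Each item is scored 1 to 5.
- Domain score = sum of 5 items / 5; subtotal = sum of 20 items / 20.
- 21 patients per group, 42 in total (Sample measurement; Abstract).

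**Step 1: item count.** 4 × 5 + 2 = 22 items, which agrees with the stated total. Removing the 2 satisfaction items leaves 20, which agrees with the divisor of the subtotal. The outcome definition is internally consistent.

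**Step 2: trying to reproduce the five levels.** A sum of k items scored 1 to 5 runs from k to 5k in whole steps, so the mean takes 5k − k + 1 = 4k + 1 distinct values, spaced 1/k apart.

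| Score | k | Possible values (4k + 1) | Step |
|---|---|---|---|
| Single item | 1 | 5 | 1 |
| Satisfaction domain (excluded) | 2 | 9 | 0.5 |
| Each analysed domain mean | 5 | 21 | 0.2 |
| Subtotal mean | 20 | 81 | 0.05 |

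Five levels arise only with k = 1. No score that the protocol reports has k = 1, and no section names a single SRS-22 item as an outcome. The description in the statistical section cannot be reproduced from any score in the outcome definition.

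**Step 3: what an ordinal model would face.** A cumulative ordinal model needs one threshold fewer than the number of categories.

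- Five categories would need 4 thresholds, but the defined scores do not have five categories.
- On the raw values, a domain mean would need up to 21 − 1 = 20 thresholds. With 42 patients that is on average 42/21 = 2 patients per possible value.
- For the subtotal the formula gives 81 − 1 = 80, but that is a ceiling. Thresholds are limited by the distinct values observed. At one visit 42 patients show at most 42 distinct values, so at most 41 thresholds.

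Such a model would be very sparse, and its treatment effect would not be a difference in SRS-22 points.

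**Step 4: consistency with the rest of the statistical section.** Summarising questionnaire data as mean and SD treats the scores as continuous. That fits the outcome definition and does not fit a single ordinal item.

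**The case against.** The strongest reply is that the protocol names only a model family. A generalized linear mixed effects model fixes no distribution or link; the family includes an identity-link model for a mean score, and the planned mean and SD summaries already point that way. This stands in part: the family is not itself an error. But the protocol contrasts this model with its linear mixed models and justifies the contrast by calling the outcome ordinal with five levels. If an identity-link model were meant, the separate sentence would have no purpose.

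A milder reading is that the sentence refers to the five response options of each item. That would imply an item-by-item analysis, which the domain and subtotal means rule out.

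Several stronger conclusions are tempting, and the document does not support them:

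- *The SRS-22 cannot be analysed as planned.* An ordinal model on the raw scores would be sparse but not impossible, and a continuous model within the named family is possible.
- *The result will be an odds ratio.* No link is stated, so this depends on a choice the protocol has not made.
- *Information will be lost by collapsing to five levels.* If scores were rounded half-up to whole numbers, all subtotals from 3.50 to 4.45 would become 4, and a change of up to 4.45 − 3.50 = 0.95 points could disappear. The arithmetic is right, but the protocol proposes no rounding, so the loss is hypothetical.
- *Eighty thresholds would be needed.* As shown in the working, that cannot arise from 42 patients at one visit.
- *The sentence was carried over from another outcome.* A reader might infer this, since the Interim analysis section cites a global rating of change from a previous study. Nothing in the document establishes it.

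**Conclusion.** The contradiction holds. The statistical section gives a false description of the SRS-22 and uses it to take the outcome out of the linear mixed models. The size of the mismatch is 5 levels stated against 21 possible values for each of four domain means and 81 for the subtotal mean. These counts rest only on the protocol's scoring rule and assume all items of a scale are answered.

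The consequence is limited. A five-category ordinal model does not match the defined scores, and an ordinal model on the raw values would be poorly supported by 42 patients. Neither makes the outcome unusable, and the data collected are the same either way. The SRS-22 is a secondary outcome; the sample size and the Cobb angle analysis do not depend on this sentence. It should be corrected before analysis.

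**What to change.** Delete the clause describing the SRS-22 as a single five-level item. Replace the sentence with one to this effect: *each of the four SRS-22 domain means and the 20-item subtotal mean will be analysed as a continuous score with the linear (mixed) model used for the other outcomes, adjusted for the baseline value of the same score, and reported as a mean difference between groups with its 95% CI.* The baseline score should be named explicitly, because it is not in the protocol's list of candidate covariables.

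If a single item was in fact intended, name the item, state the distribution and link of its model, and reconcile the section on SRS-22 dimension scores with that choice.

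Two additions are optional: naming the subtotal as the main SRS-22 measure, and a bootstrap or rank-based check in case scores cluster near the upper end of the scale. The contradiction is resolved without them.

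The cost is a change of wording. No new data, visits or patients are needed.
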